### Participants

#### Recruitment

Participants will be recruited between August 2018 and February 2019 through the Salford Royal NHS Foundation Trust acute neurology clinic service in the UK. The neurologist and specialist headache nurse will identify potential participants from their list of existing CM patients.

Details of this study will be sent to potential participants with their clinic appointment letter. Eligible participants will be female aged greater than 18 years of age, and diagnosed with CM according to the criteria of the International Classification of Headache Disorders (ICHD-III) by their neurologist. The enrolment in to tertiary care requires that patients must be free of medication over use headache and as part of the inclusion criteria (Table 2), participants will have gone through a detoxification phase and had at least one cycle of tertiary care treatment to further mitigate medication overuse headache. Exclusion criteria for this study are: contraindication to MT including spinal radiculopathy; uncontrolled psychological conditions; and any physical or MT in the last 6 weeks. Acute and abortive migraine medication will continue as usual during the study.

**Table 2 Tab2:** Inclusion and exclusion criteria

Inclusion Criteria	
• Females over 18 years of age	
• A good command of English (to enable informed consent)	
• Existing patients with chronic migraine as diagnosed by a clinical interview with a neurologist in line with the International Classification of Headache Diagnosis criteria (ICHD)	
• Undergoing care as usual from the neurologist	
• Must have had at least one cycle of treatment from neurologist and not be a new patient	
Exclusion Criteria	
• Currently having or had manual therapy to the neck or shoulder in the previous six weeks.	
• A new patient without any existing management by neurologist	
• Having a condition contraindicated for manual therapy including, but not limited to, inflammatory disorders, severe osteoporosis and tumours.	
• Identification of any medical ‘red flags’ by the neurologist.	
• Evidence of any central nervous system involvement for example:	
o Facial palsy (presence of ptosis/Horner’s syndrome)	
o Visual disturbance (presence of blurred vision, diplopia, hemianopia)	
o Speech disturbance (presence of dysarthria, dysphonia, dysphasia such as expressive or receptive)	
o Balance disturbance (presence of dizziness, imbalance, unsteadiness, falls)	

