o Paraesthesia (presence, location such as upper limb/lower limb, face)	
o Weakness (presence, location such as upper limb/lower limb)	
o Known major psychiatric or psychological conditions not under control	

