#### Intervention

The neurologist will manage the care as usual group alone. The care as usual and MT group will be managed by the neurologist and receive MT from the PI. The MT administered will consist solely of mobilisation, manipulation and soft tissue work. The PI will use a pragmatic approach to the MT administered, using any of the above manual interventions deemed clinically appropriate at each appointment based on assessment prior to treatment and participant feedback. The PI is an experienced chiropractor with over ten years’ clinical experience of chiropractic and soft tissue work, with postgraduate education and training in the management of CM. The treatment delivered will be recorded in the Case Report File (CRF). Failure to attend all manual therapy sessions will result in withdrawal from the study although provision will be made to provide an alternative appointment if the participant cannot make one as planned. Any change in a participant’s medical condition such that they fulfil the exclusion criteria above will result in their withdrawal from the study. Data from these participants would not be included in the final study results. Adverse events will be recorded in the CRF, and if classed as serious would be referred to the neurologist to be reported to the sponsor within 24 h of learning of the event and to the Main Regional Ethics Committee within 15 days in line with the required timeframe. The outline interventional procedure is shown in Table 3 with the project flow following the SPIRIT guidelines (Table 4).

**Table 3 Tab3:** Manual therapy protocol

1. Assess upper body^a^ posture in sitting	
2. Assess active and passive neck range of motion	
3. Assess shoulder girdle range of motion by raising each arm sideways from side of body up to ear	
4. Assess the temporomandibular joint	
5. Identify areas to treat in sitting position	
6. Administer MT using mobilisation, manipulation and soft tissue release in sitting position	
7. Assess patient shoulder girdle, neck and head supine and prone	
8. Administer MT in supine and prone position	
9. Following each session an outline of the MT used will be recorded.	
10. A total of 30 min will be allocated for each participant at these consultations	

^a^Upper body defined as from thoraco-lumbar junction upwards

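### Participants whose medical condition changes so that they meet the exclusion criteria are withdrawn and left out of the results, with no exemption for safety data, so new neurological signs during neck treatment may go unreported

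*Protocol article*

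**What the plan says.** The rule is in the protocol article, Methods, Intervention. The trigger is limited to changes in medical condition, and a change "such that they fulfil the exclusion criteria above will result in their withdrawal from the study". The consequence for the data follows at once: "Data from these participants would not be included in the final study results". The next sentence deals with safety: "Adverse events will be recorded in the CRF, and if classed as serious would be referred to the neurologist to be reported to the sponsor". The sponsor is to hear of a serious event in 24 hours and the ethics committee in 15 days.

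The exclusion criteria it refers back to are in the Recruitment section and Table 2. One is headed "Evidence of any central nervous system involvement for example", and its examples include facial palsy, visual disturbance, speech disturbance, "Balance disturbance (presence of dizziness, imbalance, unsteadiness, falls", "Paraesthesia (presence, location such as upper limb/lower limb, face" and "Weakness (presence, location such as upper limb/lower limb". Table 2 also lists major psychiatric or psychological conditions not under control. The Recruitment text adds spinal radiculopathy as a contraindication to manual therapy.

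The tested treatment is mobilisation, manipulation and soft tissue work, and Table 3 applies it to the neck and shoulder girdle. The Allocation section names local tenderness, aching and tiredness as potential reactions. It names no neurological sign.

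**The concern.** Entry criteria are being used a second time, after randomisation, to decide whose data count. At entry they protect participants and do not disturb the comparison. After randomisation they select on events that the treatment may have caused.

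Two things are at stake.

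- **Safety reporting.** A new neurological sign during a course of neck mobilisation or manipulation is a safety outcome. If the participant's data leave the final results, the report cannot show how often such signs occurred. The Background supports adjunctive treatment partly because it may have fewer or lesser side effects, and a report without these participants cannot test that premise.
- **The randomised comparison.** Participants who deteriorate medically may well also have poor HIT-6 scores. Removing them flatters the arm they came from. Detection may differ between arms as well. The unblinded therapist assesses manual therapy participants at five sessions (weeks 1, 2, 5, 8 and 12), and no matching series of examinations is described for the care-as-usual arm.

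**Working it through.** **1. The plan's own sample size.** Inputs from the Sample size section: difference 3.7, SD 4.91, α 0.05 (taken as two-sided), power 80%.

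- Normal approximation: 2 × (4.91 × (1.960 + 0.842) / 3.7)² = 27.6, so 28 per group.
- Two-sample t-test: 28.6, so 29 per group, as stated.
- Attrition: 29 × 1.10 = 31.9, so 32 per group, as stated. Dividing by 0.90 would give 33.

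The stated figures reproduce.

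**2. Following the rule through.** A participant develops limb weakness that is judged evidence of central nervous system involvement. She meets a Table 2 criterion through a change in medical condition, so she is withdrawn. Her data are then left out of the final results. Her event is in the case report file and, if serious, has been reported to the sponsor and ethics committee. No sentence carries it into the results. Read literally, the number of such signs in the results is zero whatever the true rate.

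**3. How likely such a case is.** The documents give no rate, so these rates are assumptions. With 32 manual therapy participants, the chance of at least one case is 1 − (1 − p)³²:

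| Assumed rate p | Expected cases | Chance of at least one |
|---|---|---|
| 2% | 0.6 | 48% |
| 5% | 1.6 | 81% |
| 10% | 3.2 | 97% |

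As a concrete case, 3 of 32 is 9.4% (exact 95% CI about 2% to 25%). On the literal reading it would appear as 0 of 29.

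**4. Effect on HIT-6.** If k of 32 participants in an arm are removed and their mean change was d points worse than that of the rest, the full-arm mean differs from the retained mean by k × d / 32. With d = 5 (assumed):

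| k removed | Shift in arm mean | Share of 3.7 |
|---|---|---|
| 1 | 1 × 5 / 32 = 0.16 | 4% |
| 3 | 3 × 5 / 32 = 0.47 | 13% |
| 6 | 6 × 5 / 32 = 0.94 | 25% |

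The between-arm bias is the difference between the two arms' shifts. It cancels if both arms lose the same number with the same deficit, and it favours manual therapy if more such participants are lost there.

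**5. Effect on power.** Same t-test, with 32 controls:

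- 32 manual therapy participants: 84%
- 29 (three removed): 82%
- 26 (six removed): 80%

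The damage is therefore to safety reporting and to the comparison, not to power.

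**The case against.** The strongest reply is that the data-exclusion sentence concerns outcome data only, with adverse events handled separately by the sentence after it. The article also commits to CONSORT, including its non-pharmacological guideline. Part of this stands: events are recorded, and serious ones are reported promptly. A reader might infer that harms would disappear altogether, and the text does not support that. But recording and expedited reporting are not the results. No sentence exempts withdrawn participants' safety data, and a general commitment to a guideline does not override a specific instruction. Even on the outcome-only reading, the HIT-6 problem remains.

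Other stronger readings also go too far:

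- **Any dizziness or tingling triggers removal.** The symptoms are examples under the heading of central nervous system involvement. A mild, passing symptom without such evidence need not trigger the rule.
- **Controls who seek outside manual therapy are dropped.** Recent manual therapy is a Table 2 criterion, but the rule is limited to a change in medical condition, and seeking treatment is not that. If that criterion did trigger withdrawal, everyone in the manual therapy arm would be withdrawn once treated, which cannot be meant.
- **There is no spare power.** The extra three per arm are there for attrition, and the power figures above show that several removals from one arm can be absorbed.

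It is also fair to say that no rate and no HIT-6 deficit can be taken from the documents. If such events are rare, the bias is small.

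**Conclusion.** The concern holds in a limited form. The protocol article states a rule that removes randomised participants from the final results because of medical changes after enrolment, and those changes include possible harms of the tested treatment. New neurological signs, above all non-serious ones, may be left out of the final results, though not out of the trial's records. The HIT-6 comparison can be biased by selective removal and by unequal detection. The direction probably favours the arm that loses more deteriorating participants.

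The size is unknown. The 0.5-point shift (13% of the target) rests on two assumptions: 3 of 32 removed from one arm only, and a HIT-6 change 5 points worse in those removed. The statement that the reported count would be zero rests on reading the exclusion sentence literally. The conclusion does not depend on an unseen statistical analysis plan, because it rests on what the article says and not on something it omits.

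**What to change.** Amend the Intervention section as follows.

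1. Delete the sentence that leaves these participants' data out of the results.
2. Separate stopping study treatment from leaving the dataset. Stopping treatment is a clinical decision and stays as it is.
3. With their consent, keep participants who stop for a medical reason in questionnaire follow-up to week 12, and analyse them in the group to which they were randomised.
4. Report all adverse events and all reasons for stopping, by arm, for every randomised participant.
5. Reconcile what remains of the withdrawal text with the adverse-event sentence, so that it is clear that recorded events reach the results.

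The cost is a wording amendment and the questionnaire follow-up of a few extra participants. The sample size does not change.

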**Table 4 Tab4:**
[figure not shown]
Project Flow Manual Therapy for Chronic Migraine

#### Outcome measures

The primary and secondary endpoints are differences in within-group changes between groups in the outcomes listed below (Table 5). These will be measured using the weekly diaries and the validated instruments in the baseline and 12-week follow-up questionnaires.

**Table 5 Tab5:** Outcome Measures

Primary Outcomes	Measurement Instrument (validity)
Migraine-related disability	Headache Impact Test (HIT 6) [54]
Secondary Outcomes	Measurement Instrument
Quality of Life	Migraine Specific Quality of Life Questionnaire (MSQ. V2.1)[59]
Use of abortive migraine medications	1.1.11.1.11.1.1Diary [69]
Percentage of participants with reduction in headache frequency (days per month) of greater than 50%	
Number of headache free days	
Stress	
Stress	Perceived Stress Questionnaire (PSS) [80]
Stress	Brief Cope [81]
Anxiety	State and Trait Anxiety Inventory (STAI-6) [63]
Anxiety & Depression	Hospital Anxiety and Depression Scale (HADS) [82]
Cutaneous Allodynia	Allodynia Symptom Checklist (ASC) [83]
Cutaneous Allodynia	Algometry [49, 84]
Patient Reported Outcome Measure	Patient Global Impression of Change Scale (PGICS) [85]

#### Data collection

All participants will be asked to complete a baseline questionnaire, comprising demographic information and the following validated instruments: Headache Impact Test (HIT6), the Migraine Specific Quality of Life Questionnaire (MSQ.V2),The perceived Stress Scale (PSS-10), State and Trait Anxiety Inventory (STAI-6),Brief Cope, Hospital Anxiety and Depression Scales (HADS) and the 12 Item Allodynia Symptom Checklist (ASC-12) The questionnaire will be available in paper or online format for completion at the initial assessment or at home at the discretion of the participant.

BMI values (from height and weight) will be calculated in the clinic and pain pressure thresholds will be taken using a somedic electronic pressure algometer [62] on each of the following muscles: Frontalis, Trapezius and Subocciptal. The order of these measurements will be taken randomly, which is an approach used in previous migraine studies [47, 48]. A distal site (forearm) will also be included to help provide a measure of wide spread central sensitisation [63]. These measures will be taken again at the end of the study after 12 weeks. Individuals assigned to the tertiary care as usual plus MT group will be given a 12 week treatment plan as recommended in IHS guidelines [52]. Sessions will be planned for Weeks 1, 2, 5, 8 and 12.The care as usual group will complete the normal 12 week cycle with the neurologist. Both groups will complete weekly diaries and an end of study questionnaire that duplicates the baseline questionnaire and includes a Patient Global Impression of Change Scale.

To encourage completion of data the participants will be encouraged to complete paper versions of the questionnaire at the first visit in the waiting area and leave it at reception, rather than taking home. Online versions will also be available. Reminder text message or emails will be sent out each week to encourage completion of the paper or online weekly diary.

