#### Allocation

A randomisation assignment sequence will be created by an independent member of the research team using randomisation software “Research Randomizer” [60]. The results will be put into sealed opaque envelopes which the participants will open in their meeting with the PI, who will explain the process to be followed depending on the group allocation.

Immediately following the initial screening by the neurologist/specialist nurse, those participants who meet the inclusion criteria will be invited to an assessment with the Principal Investigator (PI). If this is not possible, it will be arranged within 5 days. The PI will provide participants with verbal and written information about the project before gaining written consent. He will also explain the risks, and benefits as well as the potential adverse reactions to MT and how to manage them. Potential adverse reactions may include temporary local tenderness, aching and tiredness [61]. Participants will be randomised into two groups (care as usual and care as usual plus MT).

The neurologist will be blinded as to the participant’s group allocation in order to reduce initial selection and potential contact bias. The PI cannot be blind to the manual therapy group but will be blinded to the end of study survey analysis, with an independent member of the research team detailed to recode the participant reference numbers and store the key file on a password protected computer. The unblinding of single cases by the PI/CI in the course of a clinical trial will only be performed if necessary for the safety of the trial subject.

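### Participants who complete the baseline questionnaire at home or online can do so after opening their allocation envelope, so for them the primary change score may start from a HIT-6 value given with the allocation known

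*Protocol article*

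**What the plan says.** Protocol article, Allocation: the randomisation results go into "sealed opaque envelopes which the participants will open in their meeting with the PI". The same section describes an assessment with the PI, immediately after screening or within 5 days, and states: "The PI will provide participants with verbal and written information about the project before gaining written consent".

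Protocol article, Data collection: the baseline questionnaire comprises demographics, HIT-6, MSQ, PSS-10, STAI-6, Brief Cope, HADS and ASC-12. It is available on paper or online "for completion at the initial assessment or at home at the discretion of the participant". To improve completeness, participants are to be "encouraged to complete paper versions of the questionnaire at the first visit in the waiting area and leave it at reception", and that sentence presents this as preferable to carrying the form away. It is followed by: "Online versions will also be available". BMI and pressure pain thresholds are listed separately. BMI is calculated in the clinic, and no home option is given for either.

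Protocol article, Outcome measures: the primary and secondary endpoints are between-group differences in change, using the baseline and 12-week questionnaires and the weekly diaries. Under Statistical analysis, the groups are compared by Student's t test or Mann-Whitney.

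**The concern.** HIT-6 is self-reported, and participants know their arm because they open the envelope themselves. Learning that one has, or has not, been given manual therapy may change how one rates recent headache impact. If the baseline is given after that moment, any difference in reaction between the arms enters the starting value and passes straight into the change score. The starting value is then no longer protected by randomisation.

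The article's stated safeguard, under Allocation and Methodological considerations, is recoding of the data before analysis. That protects against analyst bias but has no bearing on what a participant wrote at baseline. The other instruments in the same questionnaire (MSQ, PSS, STAI-6, Brief Cope, HADS, ASC-12) are exposed in the same way.

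**Working it through.** **Order of events**

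1. Written consent is obtained by the PI (Allocation).
2. The envelope is opened in the participant's meeting with the PI (Allocation). The natural reading is that this is the same occasion as the consent assessment, although the text does not say so outright.
3. The questionnaire may be completed at home or online, as the participant chooses (Data collection). The preference for leaving it at reception over taking it away shows that home completion follows the visit.
4. No route for completing it before the visit is described. Under Recruitment, only details of the study are posted with the appointment letter, and a questionnaire completed before the visit would precede consent.
5. No visible sentence makes return of the questionnaire a condition for opening the envelope.

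Taken together, these points allow a home or online baseline to be given after allocation is known.

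**The plan's own figure**

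Inputs from Sample size: difference 3.7, SD 4.91, α = 0.05 (taken as two-sided), power 80%.

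- Normal approximation: n = 2 × (1.960 + 0.842)² × (4.91/3.7)² = 27.6, rounded up to 28 per group.
- Two-sample t test: 28.64, rounded up to 29 per group, which matches the article.

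The planned size is therefore reproduced, and the present point does not alter it.

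**Size of the possible bias**

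Let b be the differential shift in baseline HIT-6 between arms among late completers, and f the share completing late, taken as equal in both arms. Neither is given in the documents, so both are assumptions.

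- Bias in the difference in change = b × f (absolute size).
- Standard error of the difference = 4.91 × √(2/29) = 1.29, treating 4.91 as the SD of the analysed change.
- Two-sided type I error = 1 − Φ(1.96 − b×f/1.29) + Φ(−1.96 − b×f/1.29).

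| b (points) | f | Bias (points) | Share of 3.7 | Type I error |
|---|---|---|---|---|
| 1 | 25% | 0.25 | 7% | 0.054 |
| 1 | 50% | 0.50 | 14% | 0.067 |
| 1 | 100% | 1.00 | 27% | 0.121 |
| 2 | 25% | 0.50 | 14% | 0.067 |
| 2 | 50% | 1.00 | 27% | 0.121 |

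**Baseline adjustment**

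The adjusted estimate subtracts slope × baseline difference, so the bias becomes slope × b × f. With an assumed slope of 0.5 and b = 1, it is 0.5 × 0.25 = 0.125 to 0.5 × 1.0 = 0.5 points. Adjustment reduces the bias but does not remove it, because the covariate itself carries the shift.

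**The case against.** The strongest reply is that the article leaves the order unstated rather than stating a wrong one. The participant flow (Fig. 1) and the project flow (Table 4) are where consent, baseline and allocation would be set in sequence. Neither is visible in the text at hand, and either may place baseline before randomisation. Nor does the article say that the initial assessment, the first visit and the meeting with the PI are one occasion. This stands and limits confidence. It does not remove the point: if those exhibits put baseline first, a discretionary home option sits uneasily with them and has to be reconciled.

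The article also steers participants towards completion on site, so the share completing late may be small. That stands too, and it is why the bias must be scaled by f. At a 1-point shift in a quarter of participants, the type I error barely moves (0.054). But encouragement is not a requirement, and the text leaves the choice to the participant.

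A comparison of week-12 scores alone would not use the baseline. That is true, but Outcome measures defines the endpoint as change.

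A reader might infer more than the text supports:

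- **That waiting-area completion also follows the envelope.** Nothing says so. Consent, then questionnaire, then envelope fits the text equally well.
- **That every participant's baseline is a post-randomisation measure.** Only those who complete after opening the envelope are affected.
- **That a home baseline could follow the first manual therapy session.** A session is planned for week 1 and no return deadline is visible, but no text describes or implies this sequence.
- **That BMI and algometry share the problem.** No home option is given for them.

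**Conclusion.** The point holds in a limited form. As written, the article permits home and online completers to give their baseline HIT-6, and the other questionnaire scores, after learning their allocation. Those values feed directly into the primary and several secondary change scores.

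Under the illustrative assumption of a 1-point differential shift in 25% to 100% of participants, the primary comparison is biased by 0.25 to 1.0 point, or 7% to 27% of the 3.7-point target. The direction cannot be determined from the documents. The conclusion rests on reading consent and envelope opening as one meeting, and on no contrary rule appearing in Fig. 1, Table 4 or the full protocol. The documents do not support a claim that the baseline is compromised throughout, or that bias will in fact occur. The weakness is worth closing because a baseline given with knowledge of allocation cannot be recovered afterwards.

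**What to change.** State in Allocation and Data collection that the baseline questionnaire is completed and returned after written consent and before the envelope is opened. For participants who prefer to complete it at home or online, keep the envelope sealed until the questionnaire has been received. Record in the CRF the date and time of questionnaire receipt and of envelope opening. Check that Fig. 1 and Table 4 show the same order, and reconcile the home option with them.

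The cost is a slightly longer first visit, or a few days' delay in allocation for those who complete at home. The sample size stays at 29 per group, with 32 per group (64 in total) recruited, and no extra staff are needed.
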